### 5.5.3 Schedule of evaluation

|                                                   | Screening and Cohort enrollment (Study entry) | 1 week | 6 week | 3 month (Study exit) |
|---------------------------------------------------|-----------------------------------------------|--------|--------|----------------------|
| Locator info                                      | x                                             | x      | x      | x                    |
| STI and safe sex counselling                      | x                                             | x      | x      | x                    |
| HIV POC antibody test                             | x                                             |        | x      | x                    |
| Pregnancy test                                    | x                                             |        | x      | x                    |
| Behavioural risk assessment questionnaire         | x                                             |        | x      | x                    |
| Clinical assessment
(x)= only if symptomatic   | x                                             |        | (x)    | (x)                  |
| Vaginal swab for GeneXpert CT/NG and TV           | x                                             |        | x      | x                    |
| Swabs for microscopy and storage                  | x                                             |        | x      | x                    |
| Softcup and one cytobrush for cytokine assessment | x                                             |        | x      | x                    |
| Index case therapy                                | x                                             |        | x      | x                    |
| Expedited partner therapy                         | x                                             |        | x      | x                    |
| Phone follow up                                   |                                               | x      |        |                      |
| Test of Cure                                      |                                               |        | x      | x                    |

### 5.5.4 Staff training

Prior to the onset of the study, all staff will be trained about the study procedures, processes and documentation. In addition, all staff will be updated regarding the epidemiology, clinical features, diagnosis and treatment of STIs. Particular attention will be paid to the partner notification procedures and the importance of expedited partner therapy.

## 6. SAFETY

This study will enroll female participants, many of whom are at high risk of acquisition of HIV and STIs. They form a vulnerable group that is heavily affected by HIV and other health issues. Their vulnerability is also compounded by broader social determinants of health and therefore these represent important ethical concerns for participants. However, research in this population over the past two decades has been conducted with relatively little interference from the authorities. This is based largely on a model of community engagement, risk reduction, and reduction of stigma. Epidemiologic data from this province (over 50% STIs and 26% HIV prevalence) indicates that the at-risk population is large, with significant health care needs that include comprehensive HIV prevention and care services, dependable contraception and protection from sexual violence. The programme aspects of this study will address STIs in this community and how enhanced STI management may reduce HIV risk.

### 6.1 Potential risks and adequate protection against risks

Although the proposed activities pose minimal risks to participants, confidentiality will continue to be a priority and will be protected. This includes, storing all data forms in secure lockers after entry into an encrypted database with controlled access, stored data will be password protected, and program staff will be trained on research ethics. In addition, all participant interviews, focus group discussion, and surveys will take place in privacy and in appropriate locations. A unique identification system will be used to protect participant information, and at no time will the participant identifiers be shared with non-program staff. Participants who become pregnant will be referred to appropriate ante-natal care

programmes. Most importantly, any individual who wishes not to participate in research will still be able to access all of the program services without any issue.

All data generated by this project will be shared via peer-reviewed publications in a timely fashion. To protect individual patients, no identifying information will be used and reports and publication will include only summary statistics.

## **6.2 Potential benefits of the proposed research**

The participants will benefit from the study in several ways. Firstly, potential participants will be screened for STIs using point-of-care tests (the standard of care is syndromic management) and will be provided with appropriate antimicrobial treatment for themselves and their sexual contacts free of charge. Treatment may reduce the risk of pelvic inflammatory disease, chronic pelvic pain, infertility and ectopic pregnancies. In addition, all potential participants will be tested for HIV and those who are positive will be immediately referred for appropriate clinical care. Those who are HIV negative will benefit from receipt of HIV prevention services. However, the broader relevance of these data will hopefully inform policy and improve biomedical HIV prevention efforts, which represents a potential indirect benefit to society at large, even though this is a complex long-term research goal. Even if the hypotheses of the proposed research are found to be incorrect, the knowledge gained from negative data will still be important in moving the HIV field forward.

## **7. PARTICIPANT REIMBURSEMENT**

Study participants will be reimbursed as per CAPRISA Policy on Study Participant Compensation guidance considering time of visits, inconvenience of study procedures, and transport expenses. It is anticipated that the reimbursement per screening or follow-up visit will be approximately ZAR 150.

## **8. ANALYSIS**

Demographic and baseline behavioral characteristics will be described. Cytokine concentrations will be log transformed to ensure normality. Paired t-tests will be performed comparing cytokine concentrations before and after STI treatment, i.e. baseline compared to 6 weeks. Additional analysis will be performed comparing the 12 week follow-up time point to the baseline and 6 week measurements. Paired t-tests will be performed for each STI and BV and any STI, comparing baseline cytokine measurements with that measured at 6 and 12 weeks, and general linear models will be used to adjust for other STIs the participants may have. The false discovery rate method will be used to correct for multiple comparisons. In addition, longitudinal multivariate modelling approaches, which accommodate the correlation between cytokine concentrations, will be used to assess the changes in cytokine concentrations over time [73]. Data will be analyzed using SAS version 9.3 (SAS Institute Inc., Cary) and R.

The accuracy of GeneXpert STI testing will be assessed using sensitivity and specificity measures compared to the standard multiplex PCR assay for CT/NG/TV and Mycoplasma genitalium that is being used in other CAPRISA studies.

The feasibility and acceptability of GeneXpert will be determined through the administration of questionnaires to staff and participants. The quantitative variables measured in the questionnaire will be summarized and mean outcomes will be compared using t-tests, while medians will be compared using the Wilcoxon rank sum test. Categorical variables will be compared using Fisher's exact test.

When determining cure rates, the date of cure will be estimated as the midpoint between the last positive STI test date and the first negative STI test date. The focus group discussions

will be analysed for emerging themes in order to determine the feasibility and acceptability of expedited partner therapy interventions.

### Sample size calculations

The sample size is based on previous work on cytokine production associated with CT, as this is one of the commonest STIs and the cytokine patterns associated with this STI have been well quantified. The sample size was calculated to determine the minimum sample size required for a 50% reduction in mean cytokine levels after the intervention. We assume a power of 80%,  $\alpha = 0.05$  and a conservative estimate of the standard deviation as equal to the mean cytokine level in women prior to the intervention. Two scenarios were chosen for the correlation between the paired observations: moderate ( $\rho=0.6$ ) and strong ( $\rho=0.8$ ). Given that these would be in CT positive participants only, this will need to be adjusted for the proportion of women we expect to test positive for STIs to determine the number of women who will be screened. A loss to follow up rate of 10% was included (Table 4).

| Table 4. Sample Size Calculations |                 |                                               | Number to be screened, given the proportion of STIs in the population |       |       |
|-----------------------------------|-----------------|-----------------------------------------------|-----------------------------------------------------------------------|-------|-------|
| Correlation between paired data   | Number of pairs | Number of pairs (including loss to follow up) | 7.5%                                                                  | 10.0% | 12.5% |
| Moderate ( $\rho=0.60$ )          | 28              | 32                                            | 427                                                                   | 320   | 256   |
| Strong ( $\rho=0.80$ )            | 15              | 17                                            | 227                                                                   | 170   | 136   |

Based on these calculations we will screen a maximum of 427 participants. This will provide us with an estimated 32 CT positive participants. As our recruitment will be based in a STI clinic, frequented by clients at high risk for STIs, we expect that the prevalence of CT will be well over 7.5%. In order to minimize screening we will stop recruitment when we have reached 32. We expect the prevalence of NG to be  $\geq 7.5\%$ , TV  $> 20\%$  and BV  $> 50\%$ , so we will recruit all participants with NG, but only a sub-sample of participants with TV and BV. A prevalence study is about to be conducted in the PCZ CDC, which will provide us with accurate prevalence data to refine our sample size calculations before commencement. The clinic sees up to 40,000 patients with new syndromic STD per year, and we therefore do not anticipate challenges with reaching these participant numbers.

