## 2. BACKGROUND

### 2.1 Significance

STIs are strongly associated with HIV risk [8-12]. However, population based studies to manage STIs as a way of reducing HIV risk, have had limited success [13-21]. More recent evidence shows that elevated genital tract inflammatory cytokines are strongly associated with an increased risk of HIV acquisition [1, 2]. This interest in the role of cytokines in HIV acquisition has reinvigorated interest in STIs as a potential cause of inflammation, and whether novel management strategies can play a role in HIV risk reduction.

The current evidence linking cytokines to STIs and HIV risk is derived from a handful of studies. A recent study has demonstrated that in patients with CT infection the levels of granulocyte colony stimulating factor (G-CSF), interleukin (IL)-1 $\alpha$ , and regulated upon activation normal T cell expressed and presumably secreted (RANTES) were significantly higher in pre-treatment than in post-treatment endocervical secretions, whereas the endocervical levels of IL-10, IL-6, IL-1 $\beta$ , and interferon gamma-induced protein (IP)-10 were also elevated during chlamydial infection, but did not decrease after treatment [22]. Work from our own group has demonstrated that levels of chemokines and other pro-inflammatory cytokines are markedly elevated in women with STIs, whether they are symptomatic or asymptomatic [2]. In addition, several inflammatory cytokines were associated with greater risk of HIV infection. However, a recent study in commercial sex workers in Mombasa, Kenya, failed to confirm this association [23].

The convergent heterosexual epidemics of HIV and STIs are particularly evident in the South African province of KwaZulu-Natal (KZN), which is at the epicentre of the HIV epidemic. In KZN, nearly half of all new HIV infections occur in 15-24 year old women [24, 25], who are up to six times more likely to be infected than their male peers [24, 26, 27]. Although accurate and recent, population-based data are lacking, studies in KZN suggest that STIs are common. A study of 277 women attending either family planning or antenatal clinics in 2002, showed that 23% had TV, 9% CT, 6% NG and 58% bacterial vaginosis (BV) [26].

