## 5.5.2 Primary study outcome

### Inflammatory cytokine profiles as indicator of HIV risk in the female genital tract

The concentrations of 48 cytokines including pro-inflammatory cytokines, will be measured in specimen collected from the genital tract using the Softcup device. This device has already been successfully implemented in the CAPRISA 002 Acute Infection study, and has shown to be a reliable method with high acceptability among participants [72]. Cytokines will be measured at baseline, at six weeks and at three months. Based on our previous work and studies published by others on CT, the cytokines of greatest interest are G-CSF, IFN- $\gamma$ , IL-10, IL-6, IL-8, IL-1 $\alpha$ , IL-1 $\beta$ , IP-10, IL-12p70, MCP-1, MIP-1 $\beta$ , MIP-1 $\alpha$ , RANTES, TNF- $\alpha$ , TNF- $\beta$  and vascular endothelial growth factor (VEGF) [1, 2, 22]. Cytokine concentrations will be measured before and after treatment using Bio-Plex Pro Human Cytokine kits and a Bio-Plex MagPix Array Reader (Bio-Rad Laboratories). The sensitivity of these kits range between 0.2 and 45.2pg/ml for each of the 48 cytokines. While the cytokine panel included are not exhaustive, the kits strategically represent the pleiotropic and redundant nature of cytokines by including multiple cytokines involved in cellular recruitment, growth, adaptive responses, regulation, the proinflammatory response or combinations of these (Figure 3), and extends the panels of cytokines previously used to characterise biomarkers of genital inflammation that impact HIV risk [1, 2, 22].

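### Table 4's 80% power covers one unnamed cytokine at an unadjusted 0.05; it is not shown for the planned FDR-corrected analysis of up to 48 cytokines, and no primary measure is named

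*Protocol*

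**What the plan says.** **Sample size (Protocol Section 8, Sample size calculations and Table 4).** The target is the "minimum sample size required for a 50% reduction in mean cytokine levels after the intervention", with alpha 0.05 and "We assume a power of 80" per cent. The variability input is the "standard deviation as equal to the mean cytokine level in women prior to the intervention". The within-pair correlation is 0.6 or 0.8. The calculation is for CT-positive women and does not name the cytokine. Table 4 gives 28 pairs (32 with 10% loss) at correlation 0.6, and 15 pairs (17 with loss) at 0.8. Recruitment of CT-positive women stops at 32.

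**Primary outcome (Section 5.5.2).** "The concentrations of 48 cytokines including pro-inflammatory cytokines, will be measured in specimen collected from the genital tract". Sixteen of the 48 are listed as being of greatest interest, and none is designated primary. The primary objective (Section 4.1) speaks of changes in genital inflammation without tying this to a measure.

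**Analysis (Section 8).** Concentrations are log transformed. Paired t-tests compare baseline with 6 weeks, and comparisons involving 12 weeks are additional. The tests are repeated for each STI, for BV and for any STI, at 6 and 12 weeks against baseline. Then: "The false discovery rate method will be used to correct for multiple comparisons". Neither the family of tests nor the FDR level is given. Longitudinal multivariate models are planned in addition.

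**The concern.** Power, alpha and the multiplicity correction all appear in Section 8, but they describe two different analyses. The 80% is for one test at 0.05. The planned analysis is a set of tests with a threshold that is stricter than 0.05 unless nearly everything changes, run on a different scale from the one used for sizing. Under an FDR procedure, power for a given cytokine also depends on how many other cytokines truly change, and the sample size section does not address this.

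Two things are at stake. A reader of Section 8 would take 80% as the chance of detecting a halved cytokine in the analysis that will be reported, and the document does not show that. And with no primary measure, a result in which a few cytokines fall and most do not gives no rule for saying whether genital inflammation fell. That mixed pattern is plausible on the protocol's own background. Section 2.1 cites a study of CT in which three cytokines were lower after treatment, while four others "were also elevated during chlamydial infection, but did not decrease after treatment".

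**Working it through.** **1. Reproducing Table 4.** Inputs from the sample size section: mean difference 0.5 × baseline mean, SD = baseline mean, correlation ρ. Taking the same SD before and after treatment, the standardised paired effect is d = 0.5 / √(2(1 − ρ)).

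- ρ = 0.6: d = 0.5 / √0.8 = 0.559. Noncentral-t power, two-sided 0.05: 79.8% at 27 pairs, 81.4% at 28. Hence 28.
- ρ = 0.8: d = 0.5 / √0.4 = 0.791. Power is 78.1% at 14 pairs, 81.2% at 15. Hence 15.
- Loss to follow-up: 28 / 0.9 = 31.1, so 32; 15 / 0.9 = 16.7, so 17. Screening: 32 / 0.075 = 427.

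Table 4 matches exactly. The protocol does not state sidedness, but one-sided 0.05 would give 22 and 12. So the table is one two-sided test with no adjustment. At 0.05/48 = 0.00104 (the Bonferroni bound, which is also the strictest Benjamini-Hochberg step), power is 27% at 28 pairs and 22% at 15.

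**2. Same inputs with the FDR correction.** Assumptions not in the protocol: Benjamini-Hochberg at 0.05, a family of 48 (one contrast in one infection group), and every truly changed cytokine having the planned effect d = 0.559. The number changed is unknown, so a range is shown. Simulated power at 28 pairs:

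| Truly changed, of 48 | Average power per changed cytokine, independent | Same, correlation 0.5 between cytokines |
|---|---|---|
| 1 | 28% | 29% |
| 3 | 34% | 33% |
| 9 | 48% | 47% |
| 16 | 58% | 54% |
| 48 | 78% | 73% |

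Repeat simulations agree to within about two percentage points. If the family were the 16 cytokines of greatest interest, the range is 43% (1 changed) to 78% (all 16). Pairs needed for 80% average power at ρ = 0.6, with loss to follow-up in brackets: 39 (44) if 16 of 48 change, 29 (33) if all 48 change, and 60 (67) at the Bonferroni bound.

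**3. The log scale on which the tests are run.** Assume lognormal concentrations with the same coefficient of variation (CV) before and after, and ρ = 0.6 applying to the logs. Then σ = √ln(1 + CV²) and d = ln 2 / (σ√0.8). With 28 pairs and 3 of 48 changed:

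| CV | σ | d | Single test at 0.05 | Average power under FDR |
|---|---|---|---|---|
| 1 (the protocol's SD = mean) | 0.833 | 0.931 | 99.7% | about 94% |
| 2 (assumed) | 1.269 | 0.611 | 88% | about 45% |
| 3 (assumed) | 1.517 | 0.511 | 74% | about 26% |

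The protocol gives no log-scale SD, so it does not settle which row applies.

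**4. Number of tests.** The by-infection tests have two contrasts (6 and 12 weeks against baseline) in five groups (CT, NG, TV, BV, any STI): 48 × 2 × 5 = 480. Adding the overall 12 v 6 week contrast gives 480 + 48 = 528. The FDR family could therefore be as small as 16 or as large as about 528, depending on a choice the protocol does not record.

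**The case against.** **The trial may well have 80% power.** A reader might infer that the trial is underpowered. The documents do not support that. The tests are on logs, and with the protocol's own SD equal to the mean, under lognormality, power is about 94% even if only 3 of 48 cytokines change. It is 87% even at 0.05/48. The lower log-scale figures need a CV of 2 or 3, which the protocol does not state; it calls its SD assumption conservative. On the raw scale, if all 48 fall, power is about 78%, close to 80%, and Section 11 expects an overall decline. This stands, and it limits the point to a figure that is not shown.

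**The cited CT study does not fix the number changed.** Three of seven named cytokines fell. Reading that as 3 of 48 treats 41 unreported cytokines as unchanged. Scaling instead, 48 × 3/7 is about 21, with raw-scale power of about 64%. Hence the range in the table.

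**Detecting at least one change is easier.** At 28 pairs on the raw scale it is about 62% with 3 changed and 97% with 9 (51% and 76% at correlation 0.5). True, but that is not what Table 4 states, and one falling cytokine does not show that inflammation fell.

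**The plan has structure.** Baseline v 6 weeks comes first, and multivariate models are planned. The any-STI analysis will have more pairs than the CT analysis, number not given. But the first contrast is still one test per cytokine, the models are additional with no stated primary hypothesis, and Table 4 is about CT only.

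**FDR family and level can be left to an analysis plan.** Agreed; their absence is not the complaint. The complaint is that the protocol states power and a correction that do not fit together, and names no primary measure.

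**It is a proof-of-concept study.** Section 11 foresees that a null result would generate hypotheses. This lowers the severity. It does not make the stated figure apply to the planned analysis.

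**Conclusion.** The point holds in limited form. Table 4's 80% is correct for one cytokine, in CT-positive women, on the raw scale, at an unadjusted two-sided 0.05. It is not a property of the planned FDR-corrected tests on log concentrations, and the sample size makes no allowance for the correction. On Table 4's own raw-scale inputs, no scenario examined reaches 80%: average power runs from about 28% to 78% as the number changed rises from 1 to 48. On the log scale with 3 changed it runs from about 94% to 26% over CV 1 to 3. These figures rest on Benjamini-Hochberg at 0.05, a family of 48, equal effects in all changed cytokines and, for the log scale, lognormality. So the 80% is unsupported for the corrected analysis, and not shown to be missed in every case. Separately, no single measure is named to answer the primary objective. This should be fixed, but it does not invalidate the design.

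**What to change.** 1. State in Section 8 that Table 4's power covers a single unadjusted two-sided test of one cytokine in CT-positive women.
2. Give the power of the FDR-corrected cytokine-wise tests on the log scale, for a stated family and level, an assumed log-scale SD and a range of numbers of changed cytokines.
3. Before data are seen, designate one primary measure for baseline v 6 weeks in CT-positive women, tested at two-sided 0.05 with its own log-scale power. It can be one cytokine or one inflammation score, at the sponsor's choice. Keep the remaining cytokine tests as secondary under FDR.

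Table 4's power must not be said to carry over to a composite score. It assumes a 50% fall in a raw mean with SD equal to that mean, and a score has a different effect size and variance. The choice of components also matters. The nine-cytokine definition described in Section 2.3 is a top-quartile rule for at least five of nine, and it includes IL-6, IL-1β and IP-10, which Section 2.1 reports as not falling after CT treatment.

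The cost is wording and a calculation, with no extra assays; extra women would arise only if the sponsor chose to resize. Section 8 already plans to refine the sample size before commencement, although for prevalence, so there is a natural moment to do it. The downside is that the single-cytokine tests become secondary and their stated power may look less favourable.

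### Table 4's 80% power is for one uncorrected paired test, but the planned analysis corrects by false discovery rate over a primary outcome of 48 cytokines

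*Protocol*

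**What the plan says.** The Sample size calculations part of Protocol Section 8 seeks "the minimum sample size required for a 50% reduction in mean cytokine levels after the intervention". It states "We assume a power of 80" per cent, sets α at 0.05, and uses "a conservative estimate of the standard deviation as equal to the mean cytokine level in women prior to the intervention". On the pairing it says "Two scenarios were chosen for the correlation between the paired observations", namely 0.6 and 0.8. It adds: "A loss to follow up rate of 10% was included". Table 4 gives 28 pairs (32 with loss) and 15 pairs (17 with loss). Recruitment stops at 32 chlamydia-positive women.

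The primary outcome in Section 5.5.2 is a panel: "The concentrations of 48 cytokines including pro-inflammatory cytokines, will be measured". Sixteen of the 48 are listed as of greatest interest, but none is singled out as primary.

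The analysis text of Section 8 log-transforms the concentrations and runs paired t-tests of baseline against 6 weeks, then further comparisons at 12 weeks and by infection. It then states: "The false discovery rate method will be used to correct for multiple comparisons". It gives no family of tests and no FDR level.

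**The concern.** The power is computed at one significance threshold and the analysis will use a stricter one. Under a step-up FDR procedure over m tests, the p-value cut-off lies between 0.05/m and 0.05, and it reaches 0.05 only when all m tests are rejected. If few cytokines change, the cut-off sits near the strict end.

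Few changes are plausible. In the chlamydia treatment study described in Section 2.1, G-CSF, IL-1α and RANTES fell, while four other mediators "were also elevated during chlamydial infection, but did not decrease after treatment".

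What is at stake is how a negative result for an individual cytokine is read. Section 11 foresees that no reduction may be shown. A reader who takes 80% from Table 4 would give such a result more weight than the corrected test supports on Table 4's own effect size.

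**Working it through.** **1. Inputs from the protocol.** Difference = 0.5 × baseline mean; SD = baseline mean, taken as equal before and after; ρ = 0.6 or 0.8; α = 0.05; power 80%; 10% loss.

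**2. Reproducing Table 4.** The standardised effect is d = 0.5/√(2(1−ρ)).
- ρ = 0.6: d = 0.5/√0.8 = 0.559. A two-sided paired t-test (noncentral t) needs 28 pairs, with power 81.4%.
- ρ = 0.8: d = 0.5/√0.4 = 0.791. It needs 15 pairs, with power 81.2%.
- Loss: 28/0.9 = 31.1, so 32; 15/0.9 = 16.7, so 17.
- Screening: 32/0.075 = 426.7, so 427. The other screening cells also match.

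A one-sided t-test would give 22 and 12 pairs, and the normal approximation 26 and 13. Table 4 is therefore one two-sided t-test at 0.05, with no allowance for multiplicity.

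**3. The strictest step.** At 0.05/48 = 0.00104, the same noncentral-t formula gives 27% for 28 pairs (ρ = 0.6) and 22% for 15 pairs (ρ = 0.8). Reaching 80% there would take 60 and 33 pairs.

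**4. FDR power for a given truly changed cytokine.** Assumptions: Benjamini-Hochberg at 5%, d = 0.559, 28 pairs. Simulated with inter-cytokine correlation from 0 to 0.5:

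| Cytokines truly changed | Family of 48 | Family of the 16 named |
|---|---|---|
| 1 | 27% | about 40% |
| 3 | 35% | 51% |
| 7 | 43% | 63% |
| 16 | 56% | 74-78% |
| 48 | 74-78% | – |

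Correlation moves these by a few points. The top values are lower when cytokines are correlated and about 78% under independence. None reaches 80%.

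**5. Chance of detecting at least one changed cytokine of 48** (inter-cytokine correlation 0.3): about 58% if 3 change, 81% if 7 and 94% if 16.

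**6. The planned log scale.** Assume lognormal data, the same CV before and after, and log-scale ρ = 0.6; none of these is in the protocol. Then σ = √ln(1+CV²) and d = ln 2/(σ√0.8).

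| CV | σ | d | FDR power, 3 to 16 of 48 changing |
|---|---|---|---|
| 1 | 0.833 | 0.931 | 94-99% (87% at 0.05/48) |
| 2 | 1.269 | 0.611 | about 46-68% |
| 3 | 1.517 | 0.511 | about 25-46% |

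**The case against.** The strongest reply is that Table 4's effect size belongs to a raw-scale test that the protocol does not plan. With SD equal to the mean (CV = 1), lognormal data and tests on logs, power is 87% even at the strictest step. This stands, and it rules out an inference a reader might draw, that 32 women are too few. It does not rescue the printed figure: the protocol states neither a lognormal model nor a log-scale SD, and at CV = 2 or 3 the shortfall returns.

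Other points limit the consequence:

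- **Family and level.** The family of 48 and the 5% level are assumptions. Both may be set in an analysis plan not shown here, and their absence is not the criticism. A family of 16 softens the loss without removing it; a family that also spans infections and time points would deepen it.
- **What counts as a finding.** Section 4.1 asks about change in genital inflammation, not one given cytokine, and multivariate longitudinal models are also planned. A reader might infer that a true effect of the package would be missed altogether; the figures for at least one detection do not support that.
- **Population.** The 28 pairs are chlamydia-positive women only. The any-STI comparison will have more pairs, but the number is not given.
- **Favourable cases.** If all 32 women complete, power at ρ = 0.6 runs from about 35% to 85%. If ρ were 0.8, 28 pairs would give 69% at 0.05/48.
- **Evidence on non-response.** The study in Section 2.1 is titled a pilot in the reference list and used endocervical secretions, not Softcup specimens. It makes few changes plausible but does not establish that most cytokines stay put.

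**Conclusion.** The mismatch is real: the printed power refers to a single uncorrected comparison, and the printed analysis is corrected over a 48-cytokine outcome. Every cell of Table 4 reproduces, so this is not an arithmetic error; the 80% label is attached to the wrong test.

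On Table 4's effect size, with ρ = 0.6, 28 pairs and an assumed 5% FDR, power for a given changed cytokine is 27% to about 74-78% over 48 tests. It is about 35-43% if 3 to 7 change. It stays below 80% in every 28-pair case computed on that effect size.

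Whether the analysis on log values falls short depends on a log-scale SD that the protocol does not give. The finding is therefore a power statement to correct, not a demonstration that the study is underpowered.

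**What to change.** In Section 8, keep the target of 32 chlamydia-positive women and do one of two things:

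1. Restate the power for 28 pairs at the FDR-corrected threshold, on the log scale that will be analysed. Give the assumed log-scale SD and correlation, and show how power depends on the number of cytokines that change.
2. Or say plainly that 80% applies to a single uncorrected comparison.

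Optionally, make the 16 cytokines named in Section 5.5.2 the primary FDR family and treat the other 32 as exploratory. On Table 4's effect size this raises power from about 35% to 51% if 3 of the named cytokines change, and from about 43% to 63% if 7 do. The three that fell in the study in Section 2.1 are all among the 16.

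The cost is a recalculation and some wording, with no extra women. Section 8 already plans to refine the sample size before the study starts, so this can be done then. The stated power may look less favourable, and under the option claims about the other 32 cytokines become weaker.
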